#### Discontinuing criteria

4.2.3

(1)A participant wishing to withdraw from the study for any reason;(2)Serious adverse events or unusual changes in laboratory tests;(3)Patients taking another type of herbal medicine during this study.

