### Sample size

4.3

The sample will be calculated based on a previous literature study.^[11]^ The sample size observed in the Vafa's^[11]^ study was calculated on the difference in HbA1C (%) for each person between the initial and final values, resulting in: {mean of differences in the cinnamon group – mean of differences in the control group} / {2 [((SD cinnamon group) 2 + (SD control group 2)/2]} = { –0.44 –(–0.10)}/{2 [(0.722 + 0.652)/2]} = 0.4957 ≅ 0.50. So, if we consider the effect of 0.50, we need 64 participants per group (128 total) for 80% power. Although we do not expect a large loss, if we assume a 20% loss, we will need to recruit about 162 participants to have 130 participants at the end of the study. The calculations were made in GPower 3.0 by choosing the *t* test for independent samples.

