### Statistical analysis

4.6

All variables will be analyzed descriptively, with numerical and visual summaries. The 2 groups will be compared to check for differences in socioeconomic and clinical variables between the 2 groups at baseline. Numerical variables will be analyzed using the *t* test and categorical variables will be analyzed using the chi-square test.

For HbA1c analysis (in%), the change in value from baseline to end of the study will be considered as the primary endpoint and the means of both groups will be compared using the *t* test for independent groups. The significance level for this test will be 0.05. The analysis will follow the intention-to-treat principle, that is, the participant is analyzed in the group to which he was assigned, regardless of completing treatment as prescribed.

Secondary analyses will include means tests (*t* test) for numerical secondary variables, proportional tests for binary secondary variables, and chi-square test for categorical variables with more than 2 categories. Although we continue to use the significance level of 0.05, these tests will be interpreted with caution as the study was not designed to have statistical power for all of these tests. These tests will be considered exploratory.

Depending on the outcome of the primary outcome, exploratory analyzes will incorporate socioeconomic and clinical variables using regression analysis, where the final HbA1c value at the end of the study is the response variable, and the initial value, socioeconomic, and clinical variables, and the group of treatment will be the explanatory variables. Before statistical analysis, we will evaluate the amount and type of missing values. If necessary and possible, we will use multiple imputations to analyze the data. However, we will also perform the analysis with the full data and the final reports will contain the various analyzes so that the reader can compare them (sensitivity analysis).

Statistical analyses will be performed on SPSS version 25 (SPSS Inc., Chicago, IL) and Stata/SE 15.0 (Stata Corporation, College Station, TX) software for data analysis. Graphics will be done in R Studio.

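### Section 4.6 sets conditional multiple imputation beside a complete-data analysis without saying which one the primary test uses, and their comparison cannot detect loss that depends on the unseen final HbA1c

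*Protocol article*

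**What the plan says.** Section 4.6 of the Protocol article compares mean HbA1c change between arms with an independent-groups t test, by assigned group under intention to treat. "The significance level for this test will be 0.05".

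On missing values, the same section first looks at their amount and type. It then says: "If necessary and possible, we will use multiple imputations to analyze the data". An analysis of what it calls the full data, read here as participants with both HbA1c values, is to be run too, and "the final reports will contain the various analyzes so that the reader can compare them (sensitivity analysis"). Three things are not stated: what makes imputation necessary or possible, which result is primary, and any analysis that lets lost participants differ systematically from retained ones.

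Three other places bear on this:

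- Section 4.3 (Sample size) allows for loss: "if we assume a 20% loss, we will need to recruit about 162 participants". It also says that a large loss is not expected.
- Section 4.5 (Interventions and procedures) puts laboratory assessments at two visits and describes no HbA1c between them.
- Section 4.2.3 (Discontinuing criteria) lists "Serious adverse events or unusual changes in laboratory tests" among the reasons for stopping.

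**The concern.** There are two linked problems.

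First, the primary result is not identified. Two analyses of the same endpoint will be reported. If one p-value falls below 0.05 and the other does not, the text does not say which answers the trial's question.

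Second, the comparison is offered as the sensitivity analysis. Both analyses rest on missing-at-random reasoning. A participant without a 90-day HbA1c has no later HbA1c to inform the imputation, so imputed values come mainly from the baseline relation seen in those who stayed. If people who respond poorly are more likely to be lost, for reasons the recorded data do not capture, both analyses overstate the benefit by a similar amount. A reader told to compare them would see agreement and could take it as confirmation.

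**Working it through.** **Inputs from the Protocol article**

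- 4.3: mean changes -0.44 and -0.10, so a difference of -0.34; SDs read as 0.72 and 0.65. "So, if we consider the effect of 0.50", "we need 64 participants per group (128 total) for 80% power".
- 4.3: "if we assume a 20% loss, we will need to recruit about 162 participants to have 130 participants at the end of the study".
- 4.6: alpha 0.05. Sidedness is not stated; two-sided reproduces the sample size.

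**Assumed, not in the document:** baseline-to-change correlation -0.3; 20% lost in each arm; loss random in control; in cinnamon, the log odds of loss linear in the HbA1c change; imputation from arm and baseline HbA1c only.

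**Step 1. The plan's own figures**

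- Pooled SD = sqrt((0.72² + 0.65²)/2) = sqrt(0.47045) = 0.686.
- Standardised effect = 0.34/0.686 = 0.4957, rounded to 0.50.
- Two-sided t test, 80% power, effect 0.50: 63.77, so 64 per group (power 80.1%). Reproduced.
- 130/0.80 = 162.5, stated as about 162. Reproduced. That is 81 randomised and about 65 retained per arm.

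**Step 2. Loss that depends on the unseen final value**

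With a share p of the cinnamon arm lost:

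- complete-data estimate = true difference - p × (mean change of lost - mean change of retained)
- imputation estimate = true difference - p × (mean change of lost - mean of their imputed values)

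With p = 0.20 and a true difference of -0.34, large-sample values are:

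| Selection (odds ratio of loss per SD of change) | Lost minus retained | Complete-data change score | Lost minus imputed | Imputation |
|---|---|---|---|---|
| Weak (1.28) | 0.17 | -0.34 - 0.2×0.17 = -0.37 | 0.15 | -0.34 - 0.2×0.15 = -0.37 |
| Moderate (2.72) | 0.59 | -0.34 - 0.2×0.59 = -0.46 | 0.55 | -0.34 - 0.2×0.55 = -0.45 |
| Strong (4.5) | 0.78 | -0.34 - 0.2×0.78 = -0.50 | 0.72 | -0.34 - 0.2×0.72 = -0.48 |

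A simulation of 2,000 trials with 81 per arm at the moderate setting gave -0.463 (complete data) and -0.453 (imputation). With no true effect it gave -0.123 and -0.113, with false-positive rates of 18.6% and 16.6%. The two verdicts differed in only 3.8% of those null trials.

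**Step 3. Loss that depends only on baseline HbA1c, in one arm**

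With a true difference of -0.34, the complete-data change score gave -0.302 and imputation -0.338. Verdicts differed in 10% of trials. Here the comparison is informative, and it matters which result is primary.

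**Step 4. Loss completely at random**

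Verdicts differed in about 4% of trials with the planned effect. With no effect, claiming success if either test was significant gave 5.6% error against 5.0% for the complete-data test alone.

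**Step 5. What a delta shift would add**

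With 20% lost in one arm, each 0.1 HbA1c point by which lost participants are worse than imputed moves the difference by 0.2 × 0.1 = 0.02. With 65 per arm the critical difference is about 0.238. An observed 0.34 would therefore lose significance at a delta of about (0.34 - 0.238)/0.2 = 0.51. This uses the standard error in retained participants, so it is approximate.

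**The case against.** The strongest reply has five parts.

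- **The two methods do not always fail together.** A reader might infer that any link between dropout and outcome defeats both. Step 3 shows otherwise: when baseline explains the loss, imputation corrects what the complete-data change score does not. This stands, and the point is limited to loss that depends on the unseen final value given what is observed.
- **Imputation is not confined to baseline data.** Section 4.5 records adverse events, has a call every 15 days and applies an adherence test. Loss that follows a recorded adverse event could be partly explained. This stands. The calculation used baseline HbA1c alone, so it leaves out that possible gain.
- **Selective loss is not shown to be likely.** Blood results are withheld from participants until the study review is complete, no interim HbA1c is described, and stopping capsules is not said to end follow-up. Section 4.3 does not expect a large loss. A reader might take the discontinuing criteria as proof that dropout will be outcome-related, or 20% as a forecast; the document supports neither. Such loss is possible, which is the reason to test for its effect.
- **All results will be reported, and the wording can be read as letting imputation lead.** Full reporting does guard against concealment, and Step 4 shows that choosing between the two costs little type I error under random loss. A reader might infer a serious multiplicity problem; the figures do not bear that out. But imputation is itself conditional, so the deciding result remains unnamed.
- **An analysis plan may supply the detail.** The imputation model can be left there. This article, however, itself fixes the comparison and labels it a sensitivity analysis, so the label can be judged as it stands.

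**Conclusion.** The point holds in limited form. Section 4.6 leaves the primary result undefined between two analyses. It also relies on a comparison that cannot reveal bias from loss depending on the unobserved final HbA1c. In that situation the two estimates differed by 0.02 or less while both moved away from the truth by roughly 0.03 under weak selection, 0.10 to 0.12 under moderate and 0.14 to 0.16 under strong selection.

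These sizes are illustrations. They assume the full 20% allowance, selection in one arm only and imputation from baseline HbA1c. The strong case needs lost participants to be nearly 0.8 HbA1c points worse than retained ones. Smaller or more balanced loss gives less bias. The missing check for non-random loss is the main weakness; the freedom to choose between the two p-values is the lesser one.

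**What to change.** In section 4.6:

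1. Name one primary analysis: all randomised participants by assigned arm, adjusted for baseline HbA1c, with multiple imputation by arm from baseline HbA1c and other recorded data (such as adherence and adverse events) whenever the 90-day HbA1c is missing. Delete the clause that makes imputation conditional, and state that the 0.05 test applies to this result. Baseline adjustment replaces the simple t test on change and could be decided separately; a regression on baseline is already among the exploratory analyses.
2. Keep the complete-data analysis as supportive.
3. Add a sensitivity analysis that departs from missing at random, such as a delta-shift tipping point, with or without imputing lost cinnamon participants from the control arm. Control-arm imputation alone does not recover the truth: under strong selection it gives about 0.8 × -0.48 = -0.38 against a true -0.34. The tipping point shows how much worse lost participants would have to be to change the conclusion.

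The cost is a few sentences and a little programming, with no new participants or visits. The sensitivity result may be less favourable than the primary one.

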## Discussion

5

This study describes the protocol for a randomized controlled trial to evaluate the efficacy of *C verum* in reducing glycemia and lipids in people with T2DM. Facilities in using herbal medicines, especially cinnamon in this population, include feasibility for acquisition, application, and low cost. In addition, the product can easily be added to the daily lives of people with the disease.

The main contribution of this clinical trial is the development of an intervention that may be adjuvant to the current treatment already prescribed in health facilities in Brazil and around the world, allowing patients to insert a herbal product into their daily lives. In the region where the study will be conducted, the northeast region of the country, the population lacks economic resources and does not have sufficient access and coverage to health, as advocated by the World Health Organization. This study will be the first to investigate cinnamon to reduce glycemic, lipid and anthropometric levels in Brazil. In case of favorable results, this therapy may be used as an alternative or additional medicine in cases where only oral antidiabetic agents are used. In addition, nurses in their clinical practice, and by improving their activities, can promote the use of the product to minimize future complications of patients with diabetes and people who do not have the disease.
